#### Grip force

We will evaluate group differences in mean change scores on grip force. A calibrated Jamar dynamometer will be used, which is a hydraulic hand-held tool capable of measuring grip force from 0 to 90 kg. A peak hold needle retains the highest reading until the device is reset. The Swedish HAKIR manual for measuring grip force will be followed [51]. The measurement shows good test-retest, inter-tester, and intra-tester reliability [54–57].

#### Pain

For characteristics that can take on values spanning a continuum that cannot be easily measured directly, a reliable proxy measure can be obtained with a VAS ranging from 0 to 10 cm. Participants are asked to indicate the intensity of their pain symptom along a straight line measuring 10 cm. The end points of the line are labelled as the extreme lower and upper limits of the describable pain, with 10 indicating the worst possible, and 1 indicating no pain [58]. We will ask the participants how much pain they experienced in the treated hand in the last 24 h before the present assessment. The VAS which the participant is asked to mark has only the endpoints labelled with no numbers on it. On the backside of the VAS there will be numbers 0-100 mm, for the tester to register.

#### Patient global impression of change

At the four-month and one-year follow-ups, participants will be asked how satisfied or unsatisfied they are with the change in hand function compared to the situation prior to CCH treatment. The Patient Global Impression of Change (PGIC) will be used [59]. The questions for the PGIC refer to the following statement: “My hand function has changed since the collagenase treatment.” “Are you satisfied with the change?” The patients are instructed to state how satisfied or dissatisfied they are across 7 levels of satisfaction ranging from not satisfied at all to very satisfied [59].

#### Additional questions

Basic demographic information will be collected. Indications for treatment in other fingers in the same hand or in the other hand will be recorded at baseline and re-assessed at each follow-up. We will ask the participants whether they are sensitive to cold and about sick leave, both at baseline and at the follow-ups. Difficulties with oedema and scarring will be queried at the follow-ups. The participants in the intervention group will record in a diary if they have a wound, scar, or swelling; whether they used the splint and how much; and whether they used the COPM activities as exercise. The diary will be retrieved by a secretary at the four-month follow-up and the data analyst will analyse these data after the final follow-up at 1 year.

### Data management

All data collected will be entered continuously, as they become available, into SPSS (IBM SPSS Statistics for Windows, Version 22.0. Released 2013. Armonk, NY: IBM Corp) for subsequent analysis. The data will be maintained on a secure HUH research server, secured in a research database, with access granted only to the primary investigators. Identification codes of the participants and their group allocation will be kept apart from the outcomes and demographics data. Published data will be anonymised.

### Statistical analysis

We determined the appropriate sample size according to the minimal clinically important change for the COPM [44]. COPM gives two main outcomes; performance of activity, and satisfaction with performance. There is strong correlation between the two [60], and we therefore used both for the calculation of the sample size. Van de Ven-Stevens reported a standard deviation (SD) of 1.1 for performance and 0.8 for satisfaction for DC patients assessed with the COPM [47]. For this trial, we assumed a more conservative value, setting the SD to 2.0. For our power analysis, we conservatively assumed we would detect an effect only in the PIPJ group, which would produce a mean COPM difference of 1.0 between the hand therapy and control groups. Power analysis shows that we require 64 participants in each group to detect this difference for a two-sided t-test, with a significance level of *p* < 0.05 and power of 0.8. These parameters suggest we need 32 patients in each PIPJ and MCPJ subgroup. This would enable us to detect a mean difference of 2.0 (SD = 2) between PIPJ and MCPJ in the intervention group, with a power of 0.98. Assuming 20% loss-to-follow-up [22], we require 80 patients in the no hand therapy group and 80 in the hand therapy group.

Descriptive statistics will be used to characterise the participants’ data at baseline and follow-ups, and separately for the data of those participants who might drop out from the study. The baseline values of every measure will also be used to describe the randomised groups to determine their comparability.

The effect of post-CCH hand therapy at 1 year will be assessed using analysis of covariance (ANCOVA). The development of changes over time will be evaluated using a linear mixed-effects model, with time, intervention group, and their interaction as predictors. An intention-to-treat analysis will be used. The predictive value of PIPJ/MCPJ will be assessed by adding the interaction between group and PIPJ/MCPJ to the models. Results will be summarised by graphical illustrations.

The significance level is set to *p* < 0.05. SPSS and Matlab® (MATLAB and Statistics Toolbox Release 2012b, The MathWorks, Inc., Natick, MA, USA) will be used for statistical analyses and creation of Figures.

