### Hypotheses

H1. After CCH treatment for DC, patients who receive hand therapy will improve their performance of everyday activities more than those patients who do not receive hand therapy.H2. After CCH treatment for DC, patients who receive hand therapy will be more satisfied with their performance of everyday activities than those patients who do not receive hand therapy.H3. Involvement of the PIPJ in the DC is a better predictor for improvement after receiving hand therapy than involvement of only the MCPJ.H4**.** The treatment effect (hand therapy vs. control) for the COPM will be greater for patients where PIPJ is involved than for that where MCPJ solely is involved

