### Outcome measures

Recommendations for assessing treatment progress for DC will be used [42, 43]. These include a combination of generic patient-reported outcome measures (PROM), a disease-specific questionnaire, a physical measure of active and passive individual joint ROM, and grip strength, using standardised protocols for DC assessment. An overview of the measures used is presented in Table 1 together with the schedule of when they are performed. Differences in performance parameters between the two groups will be evaluated. Subgroups will be similarly evaluated. Patient performance of and self-satisfaction with performance of everyday activities 1 year after CCH treatment will be the main outcome of interest.

**Table 1 Tab1:** Schedule of enrolment, interventions, and assessments of patients with Dupuytren’s contracture

	Enrolment	Baseline tests	CCH treatment	6 weeks follow up	4 months follow up	1 year follow up
ENROLEMENT:						
Eligibility screen	X					
Informed consent	X					
Randomisation			X			
INTERVENTIONS:						
Hand therapy			X	X	X	
No hand therapy			X	X	X	X
ASSESSMENTS:						
Demographic and medical variables		X		X	X	X
Main outcome						
Everyday activities: COPM		X		X	X	X
Secondary outcomes						
Range of motion: Goniometer		X	X	X	X	X
Everyday living activities: URAM scale		X		X	X	X
Grip force: Jamar dynamometer		X		X	X	X
Pain: VAS		X		X	X	X
Cold hypersensitivity: Yes/no		X		X	X	X
Sick leave: Yes/no		X		X	X	X
Satisfaction with change in hand function: PGIC					X	X

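### Two main COPM outcomes are each tested at an undivided 0.05, with no order or success rule and no allowance for the second test in the sample size

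*Protocol article*

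**What the plan says.** In the protocol article, Statistical analysis introduces the sample size by stating that "COPM gives two main outcomes; performance of activity, and satisfaction with performance". Outcome measures gives the two scores equal standing: "Patient performance of and self-satisfaction with performance of everyday activities 1 year after CCH treatment will be the main outcome of interest". Hypotheses then separates them. H1 is that "patients who receive hand therapy will improve their performance of everyday activities more than those patients who do not receive hand therapy"; H2 is that "patients who receive hand therapy will be more satisfied with their performance of everyday activities than those patients who do not receive hand therapy". The section on the primary outcome measure confirms that a mean performance score and a mean satisfaction score are calculated separately.

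The only statement on error control is "The significance level is set to *p* < 0.05". On sample size the article says: "There is strong correlation between the two [60], and we therefore used both for the calculation of the sample size". The calculation that follows is one comparison of two means (difference 1.0, SD 2.0, two-sided 0.05, power 0.8), from which "we require 64 participants in each group to detect this difference for a two-sided t-test", raised to 80 per arm for 20% loss to follow-up. The 1-year effect is to be assessed by ANCOVA.

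**The concern.** With two main outcomes, two hypotheses and one undivided 0.05, the article does not define what a positive trial is. If performance is significant at 1 year and satisfaction is not, or the reverse, a reader cannot tell whether hand therapy has been shown to work, and the rule could be settled after the results are known. The article intends its results to guide referral policy, so this matters.

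The reason given for treating the scores together, their strong correlation, is not enough. Correlation lowers the cost of testing twice, but that cost disappears only at a correlation of 1. The published sample size is that of a single test at 0.05, so it does not automatically carry 80% power under a rule that splits alpha or requires both scores.

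**Working it through.** **Inputs.** From Statistical analysis: difference 1.0, SD 2.0, two-sided alpha 0.05, power 0.80, 64 evaluable per arm, 20% loss, 80 randomised per arm; cited SDs of 1.1 (performance) and 0.8 (satisfaction). The correlation is described only as strong. I assume 0.7 to 0.95 for the two test statistics; this range is not in the article.

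**1. The article's own figure.** Normal approximation: n per arm = 2 × (1.960 + 0.842)² × 2.0² / 1.0² = 62.8, so 63. The t-test solution is 63.8, so 64. Allowing for loss: 64 / 0.80 = 80. Both figures reproduce. Power at 64 per arm is 0.801 (t-test). One SD, above both cited values, and one difference serve both scores, so this is the power for performance alone and equally for satisfaction alone.

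**2. If either score suffices.** Under no effect on either score, with Z1 and Z2 standard bivariate normal with correlation ρ, the chance of at least one false positive is P(|Z1| > 1.96 or |Z2| > 1.96).

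**3. If both must be significant.** The chance of a false claim cannot exceed 0.05, since each test must itself pass at 0.05. The cost is power. The noncentrality is 1.0 / (2.0 × √(2/64)) = 2.83, and joint power is P(Z1 > 1.96 and Z2 > 1.96) with both means at 2.83 (normal approximation, under which power for one score is 0.807).

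| Assumed ρ | Either suffices: chance of ≥1 false positive | Both required: joint power at 64 per arm | Both required: n per arm for 80% |
|---|---|---|---|
| 0.7 | 8.3% | 0.72 | 76 |
| 0.8 | 7.8% | 0.74 | 74 |
| 0.9 | 7.0% | 0.76 | 71 |
| 0.95 | 6.5% | 0.77 | 69 |

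For reference, independence would give 1 − 0.95² = 9.75%. The article's own description of the correlation makes that case irrelevant.

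**4. If alpha is split equally (0.025 each).** The t-test needs 77.3, so 78 evaluable per arm, and 78 / 0.80 = 97.5, so 98 randomised. At 64 per arm, power per score falls from 0.80 to 0.71.

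**5. Sensitivity to the residual SD.** The power figures in steps 3 and 4 depend on SD 2.0 and no covariate adjustment. If ANCOVA adjusts for baseline and the baseline correlation is about 0.44 (assumed), the residual SD is 2.0 × √(1 − 0.44²) = 1.80. Then 64 per arm gives 0.81 per score even at 0.025. The noncentrality becomes 1.0 / (1.8 × √(2/64)) = 3.14, and joint power at 0.05 each is 0.82 to 0.86 over the same ρ range. At the cited SDs of 1.1 and 0.8, power per score exceeds 0.99 even at 0.025. The false-positive figures in step 2 do not depend on the SD.

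**The case against.** The strongest reply has three parts.

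First, a reader might infer that the trial's false-positive rate is above 5% as the plan stands. The text does not support that. The excess arises only if a win on either score is enough, and the article never says so. The abstract and Outcome measures refer to a main outcome in the singular, which is compatible with requiring both, and H1 and H2 can be read as two distinct claims rather than two routes to one verdict. This stands: the inflation is conditional. What remains is that the article leaves the condition open.

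Second, a reader might infer that the sample size covers only one of the two scores, and that the sentence about using both should be struck out. That is wrong. An SD is cited for each score, the planning SD exceeds both, and the same calculation applies to each. The sentence is compatible with the arithmetic; what it lacks is any allowance for testing twice. The planning SD is also described as conservative and the planned analysis is ANCOVA, so the power shortfall may be small or absent. This stands too.

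Third, testing order is often left to a statistical analysis plan, which may exist and is not shown, and a journal article is condensed. This stands only in part. The article itself fixes two main outcomes, an undivided 0.05, a sample size, and correlation as the reason for treating the scores together. A later plan that split alpha or required both would no longer correspond to the power stated here.

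**Conclusion.** The point holds in a limited form. The article gives two main outcomes separate hypotheses at an undivided 0.05 and does not say how they combine. The 64 per arm is correct for each score singly and makes no provision for testing both.

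The size depends on the rule eventually adopted. For assumed correlations of 0.7 to 0.95, the chance of at least one false positive is about 8.3% to 6.5% if either score suffices. If both are required, error is controlled and joint power is about 0.72 to 0.77, given SD 2.0 and an unadjusted t-test. The power loss could vanish with a smaller residual SD. The false-positive excess under an either-score rule would not. Settling the rule in advance is a worthwhile improvement at little cost; the calculation as published contains no numerical error on this point.

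**What to change.** Prespecify a fixed order for the two 1-year analyses. For example: test performance (H1) at two-sided 0.05, and test satisfaction (H2) at two-sided 0.05 only if H1 is significant. The article gives the scores equal standing, so which goes first is the investigators' choice; it must be made before the outcome data are seen.

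Keep the statement that both scores informed the sample size, but reword it to say that 64 evaluable per arm gives 0.80 power for each score singly, and therefore for the first test in the order. H4 refers to the COPM without saying which score, so either label the interaction hypothesis secondary or name its score.

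The cost is wording only: 64 evaluable and 80 randomised per arm are unchanged, and the error across H1 and H2 is held at 5%. The downside is that the second score cannot be claimed as confirmatory if the first fails, and the chance of confirming both remains the joint power shown in the working. If the investigators prefer to require both scores or to split alpha, they should say so and restate the power or sample size to match.

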### Randomisation and blinding

Included participants will be allocated to the four groups by a block randomisation method, stratified for PIPJ affection in one or more of the treated fingers, and MCPJ contractures (without PIPJ affection in any of the treated fingers). The randomisation schedule will be prepared using software by an independent statistician not involved in the study. The project group will be blinded for the block size. The assignment to either the hand therapy group or the control group will be put in sealed opaque envelopes with numbers, following an order generated by the software. A list with the numbers of the envelopes will be marked when the envelopes are used. The list and envelopes will be stored in a private locked closet that is inaccessible to blinded study researchers. The envelope will be opened by the participant and a receptionist when the CCH treatment is finished. If the participant is allocated to the hand therapy group, the therapy starts at the day of the extension procedure. The surgeon is also blind to participant allocation, since the CCH treatment is finished before allocation. It is not possible for the therapist performing the hand therapy intervention to be blinded, but the person performing and managing the assessments will be blinded. The participant will be instructed not to inform the assessor of their allocation group, nor to reveal any related aspects during any of the assessments. By nature of PIPJ and MCPJ DCs, it is impossible to blind this subgroup allocation.

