### Intervention

#### All participants

Participants in the two groups are all treated with a collagenase injection (i.e., CCH) and extension procedure. A needle fasciotomy is done in addition in the same procedure for a few. These will be marked, and considered as an adjustment variable in the analysis. If the extension procedure causes a wound, it is dressed, and the patient is informed on how to prevent infection. An employer sick note is provided if needed. Further intervention depends on group assignment.

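### PIPJ/MCPJ involvement stratifies the randomisation but is not named as a covariate in the analysis models; adding it is free and avoids a test that may be conservative

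*Protocol article*

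**What the plan says.** Under Randomisation and blinding, participants are "allocated to the four groups by a block randomisation method, stratified for PIPJ affection in one or more of the treated fingers", the other stratum being MCPJ contracture without PIPJ involvement.

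The Statistical analysis section describes three pieces of modelling:
- The 1-year effect of hand therapy is assessed by ANCOVA. No covariates are listed.
- Change over time is assessed by a linear mixed-effects model "with time, intervention group, and their interaction as predictors".
- For the joint subgroups: "The predictive value of PIPJ/MCPJ will be assessed by adding the interaction between group and PIPJ/MCPJ to the models".

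Other sections do name adjustment variables. Under All participants, on needle fasciotomy: "These will be marked, and considered as an adjustment variable in the analysis". Under Participants, Dupuytren treatment of other fingers or of the other hand, and CRPS or infection, are treated in the same way. PIPJ/MCPJ is not named as a main effect or adjustment variable anywhere.

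H4 states that the effect of hand therapy versus control on the COPM "will be greater for patients where PIPJ is involved than for that where MCPJ solely is involved".

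**The concern.** When allocation is balanced within strata, the between-stratum part of the outcome variance cannot contribute to the difference between arms. A model without the stratum still counts that part as residual noise. The treatment estimate is not distorted, but its reported standard error is too large, the test rejects less often than its nominal level, and some power is lost. This happens only if the stratum predicts the outcome beyond the other covariates.

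A second, lesser matter is the description of the subgroup analysis. It names the interaction to be added but not the stratum main effect. If the main effect were left out, the interaction coefficient could pick up a prognostic difference between joint types instead of the difference in treatment effect that H4 concerns.

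**Working it through.** **Inputs from the protocol (Statistical analysis).** Difference between arms 1.0 COPM point; SD 2.0; two-sided 5% level; power 0.8; 64 evaluable per arm; 32 per subgroup cell; 20% loss to follow-up.

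**The plan's own figures.** The normal approximation gives n = 2 x (1.96 + 0.842)^2 x 2^2 / 1^2 = 62.8, so 63 per arm; the exact t-test gives 63.77, so 64. Allowing for loss, 64 / 0.8 = 80 per arm and 32 / 0.8 = 40 per cell. All agree with the protocol.

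**Assumption.** The documents give no outcome difference between PIPJ and MCPJ-only patients. Call it g and let it run from 0 to 2 COPM points, equal in both arms. Take 2.0 as the within-stratum SD, with equal strata.

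**Standard error of the treatment effect.**
- Stratum included: 2 x sqrt(2/64) = 0.354 for every g.
- Stratum omitted: the residual SD becomes sqrt(4 + g^2/4). At g = 1 this is 2.06, SE 0.364, ratio 1.03. At g = 2 it is 2.24, SE 0.395, ratio 1.12.

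**Type I error and power, analytically.** The estimate still varies with SD 0.354, so the actual level is 2 x (1 - Phi(1.96 x ratio)): 0.043 at g = 1 and 0.028 at g = 2. Power for a 1.0-point effect is about Phi((1 - 1.96 x SE) / 0.354):
- g = 1: (1 - 0.714) / 0.354 = 0.81, power 0.79.
- g = 2: (1 - 0.775) / 0.354 = 0.64, power 0.74.

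**Simulation (5,000 trials per row, 32 per cell, least squares, no other covariates).**

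| g | SE, stratum omitted | Type I error, omitted | Power, omitted | Power, included |
|---|---|---|---|---|
| 0 | 0.353 | 4.7% | 0.80 | 0.80 |
| 0.5 | 0.355 | 4.6% | 0.80 | 0.80 |
| 1 | 0.364 | 4.1% | 0.78 | 0.80 |
| 1.5 | 0.377 | 3.6% | 0.76 | 0.80 |
| 2 | 0.395 | 3.1% | 0.73 | 0.80 |

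With the stratum included, type I error is about 5% throughout.

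**If 2.0 is the overall SD instead.** The within-stratum SD at g = 1 is sqrt(4 - 0.25) = 1.94. The SE with the stratum included is 1.94 x sqrt(2/64) = 0.342, and power is Phi(1/0.342 - 1.96) = 0.83. The unadjusted analysis then still delivers the planned 0.80, and including the stratum adds to it.

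**Interaction with and without the stratum main effect (no true interaction).**
- Both main effects included: the estimate is unbiased and rejection is about 5%.
- Main effect dropped, arms and strata coded 0/1 with control as 0: the coefficient is the PIPJ-minus-MCPJ difference within the therapy arm and so has expectation g. At g = 1 its SE is sqrt(4.125 x 2/32) = 0.508, z is about 1.97, and rejection is about 50% (52% simulated).
- Main effect dropped, -1/+1 coding: the estimate is unbiased, with rejection of 4.0% at g = 1 and 3.0% at g = 2.

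**Limit of the check.** These figures are for a single comparison at 1 year. In the mixed model, a stratum difference that is constant over time cancels from within-patient changes, so the size there depends on the covariance structure and on how far the difference varies over time. That was not calculated.

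**The case against.** The strongest reply is that this is an article, and an article may leave a covariate list to the full protocol or analysis plan. For the 1-year ANCOVA that reply stands: no covariates are listed, so the text is silent about the stratum and does not exclude it. The list in the Statistical analysis section is also incomplete by the article's own account, since adjustment variables named elsewhere are not repeated there. What remains is that the mixed-model predictors are listed without the stratum, and that the article takes the trouble to name several adjustment variables but not the one used in the randomisation.

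It can also be said that the harm is small. That stands too. There is no bias, the error is in the conservative direction, it vanishes if the stratum is not prognostic, and a baseline COPM covariate could reduce it further. The trial was sized for an unadjusted t-test, so if 2.0 is the overall SD there is no shortfall against the plan.

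A reader might infer more: that the H4 test is confounded with prognosis and would produce a false positive about half the time. The documents do not support this. The figure needs three things that they do not state: that the stratum main effect is really dropped, that 0/1 coding is used, and that a 1-point prognostic gap exists. Adding an interaction is ordinarily shorthand for a model that keeps its lower-order terms. The two-by-two layout under Design and the wording of H4 favour that reading. The power statement for PIPJ versus MCPJ within the intervention group might seem to point the other way, but it is a sample-size statement and does not specify a model.

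**Conclusion.** The point holds as a free improvement. The stratification factor is absent from the listed mixed-model predictors and is not named as an adjustment variable for the ANCOVA. The cost of leaving it out runs from nothing, if joint involvement is not prognostic, to an SE about 12% too large and power of about 0.73 at an assumed 2-point difference. At 1 point it is about 3% and 0.78. These sizes rest on the assumed difference, on 2.0 being the within-stratum SD, on 32 evaluable patients per cell and on there being no other covariates. The treatment estimate is unbiased throughout, and false positives become rarer, not more frequent.

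The interaction part is a request for clarification. The sentence does not settle whether the stratum main effect is in the model, and no error is demonstrated there.

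**What to change.** 1. State that PIPJ/MCPJ stratum, as used in the randomisation, is a fixed covariate in the 1-year ANCOVA and, together with stratum x time, in the mixed model.
2. For H4, state that the ANCOVA contains group, stratum and group x stratum. State that the mixed model contains group x stratum x time with all lower-order terms, read at 1 year. Report the interaction and the treatment effect within each stratum.
3. Take the overall treatment effect from the model without group x stratum, so that it does not become the effect in one reference stratum.

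The cost is wording. The stratum is already recorded for every participant, the planned 80 per arm does not change, and the main ANCOVA loses one degree of freedom. With time as a four-level factor, the mixed model gains 1 + 3 = 4 parameters for stratum and stratum x time. The change should be fixed before the outcome data are analysed by group.
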